| Process of Care Measures                                       |                     |                       |                       |                                       |                     |
| Duration of time with open chest post-operatively median (IQR) |                     |                       |                       |                                       |                     |
| Treated with inhaled Nitric Oxide post-operatively n (%)       |                     |                       |                       |                                       |                     |
| Duration of inhaled Nitric Oxide median (IQR)                  |                     |                       |                       |                                       |                     |
| Treated with renal replacement post-operatively n (%)          |                     |                       |                       |                                       |                     |
| Duration of renal replacement median (IQR)                     |                     |                       |                       |                                       |                     |
| Physiological Descriptors                                      |                     |                       |                       |                                       |                     |
| Organ dysfunction post-operatively (PELOD-2)                          |                     |                       |                       |                                       |                     |
| PICU admission median (IQR)                                    |                     |                       |                       |                                       |                     |
| 24 hours median (IQR)                                          |                     |                       |                       |                                       |                     |
| 48 hours median (IQR)                                          |                     |                       |                       |                                       |                     |
| Troponin post-operatively                                             |                     |                       |                       |                                       |                     |
| PICU admission median (IQR)                                    |                     |                       |                       |                                       |                     |

|                                                  |  |  |  |  |  |
|--------------------------------------------------|--|--|--|--|--|
| 24 hours post-PICU admission median (IQR) |  |  |  |  |  |
| Creatinine                                       |  |  |  |  |  |
| PICU admission mean (SD)                  |  |  |  |  |  |
| 24 hours post-PICU admission mean (SD)    |  |  |  |  |  |
| Acute kidney injury: PICU admission n (%) |  |  |  |  |  |
| Stage 1 n (%)                             |  |  |  |  |  |
| Stage 2 n (%)                             |  |  |  |  |  |
| Stage 3 n (%)                             |  |  |  |  |  |
| Acute kidney injury: 24 hours n (%)       |  |  |  |  |  |
| Stage 1 n (%)                             |  |  |  |  |  |
| Stage 2 n (%)                             |  |  |  |  |  |
| Stage 3 n (%)                             |  |  |  |  |  |
| Acute kidney injury: 48 hours n (%)       |  |  |  |  |  |
| Stage 1 n (%)                             |  |  |  |  |  |
| Stage 2 n (%)                             |  |  |  |  |  |
| Stage 3 n (%)                             |  |  |  |  |  |

395 SD standard deviation; IQR interquartile range; ECLS extracorporeal life support; PICU paediatric intensive care unit; CI confidence interval  
396

397 **Supplementary Appendix**

398

399 **S1. List of approved protocol modifications**

400

| Version Number | Approval Date | List of Modifications                                                                                                                                                                                                                                                                                                                                                                                                                                                                                                                                          |
|----------------|---------------|----------------------------------------------------------------------------------------------------------------------------------------------------------------------------------------------------------------------------------------------------------------------------------------------------------------------------------------------------------------------------------------------------------------------------------------------------------------------------------------------------------------------------------------------------------------|
| 1 (Original)   | 06/03/2017    | -                                                                                                                                                                                                                                                                                                                                                                                                                                                                                                                                                              |
| 1.1            | 16/07/2017    | 
 
• Addition of study sites (Children's Hospital Westmead, Sydney; Perth Children's Hospital)
 
• Addition of investigators
 
• Inclusion of planned secondary analyses
 
• Change to randomisation stratification
 
• Inclusion of additional exclusion criteria
 
• Consent form modification
 
• Further detail on instructions on gas flow across all sites, safety cut offs (Met Hb)
 
• Further detail on data collection and blood sampling procedures
 
 |
| 1.2            | 20/11/2017    | 
 
• Addition of study site (Utrecht Medical Centre, The Netherlands)
 
• Clarification on censoring outcomes at 28 days
 
• Inclusion of additional exclusion criteria
 
• Further detail on consent processes
 
                                                                                                                                                                                                                                                                            |
| 1.3            | 18/07/2018    | 
 
• Addition of neurodevelopment assessment with funding infrastructure
 
• Addition of socioeconomic Survey
 
• Addition of hyperoxia as pre-planned analyses
 
• Revision of study sample size
 
                                                                                                                                                                                                                                                                                          |
| 1.4            | 10/10/2018    | 
 
• Updating information on Queensland Children's Hospital
 
• Accessing medical records from other healthcare facilities
 
• Blood collection for inflammatory biomarkers optional on consent form
 
                                                                                                                                                                                                                                                                                              |

401

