**Details on Pilot Data and Limitation of the Pilot Data:** We have performed a single institution pilot trial at RCH Melbourne for this study to investigate feasibility and safety of the NO delivery in infants and children (0-16 years) undergoing CPB. In this pilot trial we allocated children to receive NO delivered into the oxygenator of the CBP machine versus control. NO was delivered at 20 ppm during the entire length of CPB. The primary outcome was feasibility and safety as well as a reduction of LOCS. The pilot study was performed in a single institution (Royal Children's Hospital Melbourne, HREC 33112B, RCH Melbourne), which is the largest paediatric cardiac surgical service in ANZ. The pilot data showed several important findings, which helped us to strengthen and improve the protocol for this proposal: children aged > 2 years showed little benefit from the NO as an intervention and stratifying the children in 0-28 days and 29days-2 years showed a greater difference in the clinically relevant outcomes such as length of mechanical ventilation (compared to the original <6 weeks, 6 weeks to 2 years). This age group <28 days is commonly associated with very different types and high risk of cardiac surgical procedure. The pilot study showed overall a significant reduction of the incidence of LCOS. Since there is no accepted standard definition of LCOS the generalisability of the results can be disputed. Table 1 shows the re-analysed results for age group 0-2 years.

Post hoc analysis restricted to the age group < 2 years showed stratifying the children in 0-28 days and 29days-2 years demonstrated a greater difference in the clinically relevant outcomes such as length of mechanical ventilation compared to the original <6 weeks, 6 weeks to 2 years) (**Table 1**). In addition, this age group <28 days is commonly associated with high risk cardiac surgical procedures.

335

| Outcome           |          | n   | control             | NO on bypass       |
|-------------------|----------|-----|---------------------|--------------------|
|                   |          |     | Mean (CI)           | Mean (CI)          |
| PICU              | all      | 132 | 187.4 (120.7-254.2) | 133.6 (87.4-179.8) |
| Length of stay    | <28days  | 63  | 171.7 (119.4-224.0) | 161.3 (80.9-241.8) |
| (hrs)             | 29d-2yrs | 69  | 199.2 (86.4-312.1)  | 107.5 (56.3-158.6) |
| Length of         | all      | 130 | 97.8 (61.5-134.1)   | 65.1 (45.5-74.6)   |

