### 7.2 Data Collection

Baseline variables, primary end points, secondary end points, pre-determined physiological variables of interest, and process of care measures will be prospectively recorded into a study REDCap online database.

**Time Points for Data Collection.** All physiological and blood parameters are captured for the first 48 hours post operatively and analysed (for patients discharged earlier only data up to discharge will be collected). The specific time points for these parameters will be: on admission to PICU (within the 1st hour), 6 hours, 12, 24, 36 and 48 hours post admission (or until PICU discharge). Gross functional performance assessment will be recorded on admission to PICU and upon discharge from PICU and discharge from hospital. Follow-up to define neurological/functional outcome and quality of life (including phone interviews with parents/caregivers) will be performed at 6-12 months postoperatively.

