## **Outcome measures**

The definition and detail of calculation of outcome measures can be found in the Supplementary Appendix (Section S2), alongside the Stata scripts written to calculate these outcomes (available on GitHub (16)). Briefly, the outcomes are:

- Primary outcome measure: VFDs within 28 days from start of CPB
- Secondary outcome measures:

- Individual VFD components (i.e. duration of mechanical ventilation, death within 28 days after CPB start)
- Individual and components of composite measure of LCOS, and/or ECLS within 48 hours after CPB start and/or death within 28 days after CPB start;
- Length of PICU stay after CPB start;
- Length of hospital stay after CPB start;
- Process of care measures:
  - Treatment with ECLS within 48 hours after CPB start;
  - Duration of postoperative time spent with open chest including unplanned chest reopening after CPB start;
  - Treatment and duration of treatment using inhalational nitric oxide postoperatively after CPB start;
  - Treatment and duration of treatment of postoperative renal replacement therapy (includes peritoneal and continuous venous-venous haemodialysis) after CPB start;
- Physiological descriptors:
  - Postoperative troponin levels during the first 24 hours postoperatively;
  - Severity and duration of postoperative organ dysfunction; and
  - Postoperative acute kidney injury (AKI) and serum creatinine levels measured during the first 24 hours.

For the purposes of analysis and reporting, LCOS within 48 hours after CPB start, ECLS within 48 hours after CPB start, death within 28 days after CPB start and length of stay in PICU and hospital are classified as potentially patient-important secondary outcomes. The remaining secondary outcomes will be reported to describe patient physiology and processes of care only.

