#### **List of planned figures**

**Figure 1.** CONSORT participant flow diagram

**Figure 2.** Cumulative incidence functions for extubation (accounting for mortality) (all patients, and the pre-specified subgroups)

**Figure 3.** Composite figure of a) bar chart depicting proportion of patients with LCOS, b) mean (and 95% CI) SaO2-ScvO2 difference, c) boxplot of lactate levels, d) boxplot of VIS score, e) mean (and 95% CI) of creatinine values, over time points 0, 6, 12, 24, 48 hours after PICU admission, f) PELOD-2 score at 0, 24, 48 hours after PICU admission, separated by treatment group

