Process of care measures will include the use of ECLS (as defined above); duration of time with open chest post-operatively within the first 28 days (as all surgeries will have an open chest during theatre, the time measure will start with admission to PICU, and will include time spent with open chest in cases of emergency secondary reopening); treatment and duration of treatment with inhalational NO from admission to PICU post-operatively within the first 28 days; and treatment and duration of treatment with renal replacement from admission to PICU post-operatively within the first 28 days (defined as the use of peritoneal dialysis or continuous renal replacement therapy [CRRT]). Duration of treatment with inhalational NO post-operatively and duration of treatment with renal replacement post-operatively will be restricted to those patients receiving these treatments.

433 Organ dysfunction will be assessed at admission to PICU, after 24 hours and after 48 hours, and will be defined by using the cardiovascular, respiratory,  
434 renal, neurological, and haematological components of the Paediatric Logistic Organ Dysfunction-2 (PELOD-2) scores (24). If score items are missing  
435 then it will be assumed that value was normal for the purpose of the score.

436

437 Postoperative Acute Kidney Injury was assessed using serum creatinine levels to classify according to Kidney Disease: Improving Global Outcomes  
438 (KDIGO) criteria (25). Because no baseline creatinine values were available, we applied the age-specific thresholds used in PELOD-2 to define the  
439 presumed baseline creatinine values. KDIGO Stage 1 was defined as an increase in creatinine to 1.5 to 1.9 times the presumed baseline; Stage 2 as an  
440 increase 2.0 to 2.9 times; and KDIGO 3 as an increase  $\geq 3.0$  baseline and/or the use of RRT.

441

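### The SAP does not settle when acute kidney injury is assessed or who is counted at 48 hours, so the 48-hour comparison may rest only on children still in PICU

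*Combined protocol and SAP*

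**What the plan says.** Four places in the SAP bear on the AKI window, and they do not agree.

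- **Outcome measures, physiological descriptors:** "Postoperative acute kidney injury (AKI) and serum creatinine levels measured during the first 24 hours".
- **Table 3:** AKI by stage at PICU admission, at 24 hours and again at "Acute kidney injury: 48 hours". The table is labelled intention-to-treat and has columns for an unadjusted p-value, a difference with 95% CI, and an adjusted p-value. Its creatinine rows stop at 24 hours.
- **List of planned figures, Figure 3e:** creatinine "over time points 0, 6, 12, 24, 48 hours after PICU admission".
- **Supplementary Appendix S2:** "Postoperative Acute Kidney Injury was assessed using serum creatinine levels to classify according to Kidney Disease: Improving Global Outcomes", with renal replacement also counting as stage 3. No assessment times are given.

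On data collection, Protocol 7.2 says "All physiological and blood parameters are captured for the first 48 hours post operatively and analysed", but "for patients discharged earlier only data up to discharge will be collected".

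On missing values, S2 evaluates LCOS up to PICU discharge and treats missing items as no LCOS. It treats missing PELOD-2 items as normal. Imputation (SAP, Treatment of missing data) covers the primary outcome only. AKI has no rule.

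**The concern.** A child who leaves PICU on the first or second day has no study creatinine at 48 hours. The SAP analyses binary secondary outcomes by logistic regression. With no rule for a missing outcome, that model drops the child. The 48-hour odds ratio would then compare children still in PICU, and membership of that group is decided after randomisation. Protocol 2.2 lists a shorter PICU stay as an aim of NO, so the denominator may itself depend on treatment.

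If the children who leave early are the well ones, the arm that discharges faster loses more well children. Its AKI percentage then rises without any true effect on the kidney. The result would still appear in an intention-to-treat table with an estimate and p-values.

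**Working it through.** The plan states no figure for children without a 48-hour value, so there is nothing to reproduce. The size has to be built on assumptions.

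**Inputs**
- Pilot PICU stay, children under 2 years (Protocol 2.1, Table 1): control mean 187.4 h (95% CI 120.7–254.2), NO 133.6 h (87.4–179.8), 132 children in all.
- Pilot arm sizes (assumed): 67 control and 65 NO. They sum to 132, and 24/67 = 35.8% and 8/65 = 12.3% match the pilot LCOS rates.
- Trial size: 660 per arm (SAP, Sample size).
- Shape of the stay distribution and the true AKI rate at 48 hours: not in the documents, so varied below.

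**Step 1: SD of stay from the CI**, SD = (half-width / t) × √n.
- Control: 66.75 / 1.997 × √67 = 273.7 h.
- NO: 46.2 / 1.998 × √65 = 186.4 h.

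**Step 2: share m discharged before 48 hours.**
- Exponential: 1 − exp(−48/187.4) = 22.6%; 1 − exp(−48/133.6) = 30.2%.
- Lognormal, with σ² = ln(1 + (SD/mean)²) and μ = ln(mean) − σ²/2. Control: (3.871 − 4.662)/1.069 = −0.740, giving 23.0%. NO: (3.871 − 4.354)/1.040 = −0.465, giving 32.1%.
- Weibull and gamma, matched to the same mean and SD: 36.5% and 42.2%; 40.2% and 44.5%.

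Averaged over two equal arms, this runs from about 26% (exponential) to 42% (gamma).

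**Step 3: only children with a value are analysed.** Let both arms have the same true AKI rate p, and let q be the rate among discharged children. The observed rate is (p − mq)/(1 − m).

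Lognormal, p = 10%, q = 0: control 0.10/0.7705 = 0.1298; NO 0.10/0.6789 = 0.1473. The odds ratio is (0.1473/0.8527)/(0.1298/0.8702) = 1.16. Each arm has 66 AKI cases, with 442.5 and 382.1 children without AKI. SE = √(1/66 + 1/66 + 1/442.5 + 1/382.1) = 0.188, and ln(1.158)/0.188 = 0.78.

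Spurious odds ratio at p = 10%:

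| Shape | q = 0 | q = p/2 | q = p |
|---|---|---|---|
| Exponential | 1.13 | 1.07 | 1.00 |
| Lognormal | 1.16 | 1.09 | 1.00 |
| Weibull | 1.12 | 1.07 | 1.00 |
| Gamma | 1.09 | 1.06 | 1.00 |

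At p = 20% (lognormal, q = 0) the rates are 26.0% and 29.5%, a gap of 3.5 points. The odds ratio is 1.19; SE = √(2/132 + 1/376.5 + 1/316.1) = 0.145, so the bias is 1.2 SE. At p = 30% the gap is 5.3 points.

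**Step 4: missing counted as no AKI.** The observed rate is p − mq. With q = 0 there is no bias. At p = 20% (lognormal) the NO-minus-control difference is −0.9 points if discharged children have half the average rate (17.7% and 16.8%) and −1.8 points if they have the same rate (15.4% and 13.6%). For p from 10% to 30% over the exponential, lognormal and gamma shapes, the range is 0 to −2.7 points. This favours the faster-discharged arm.

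The two readings of the same rows therefore differ in sign, and the SAP does not choose between them.

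**The case against.** The strongest reply has four parts.

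*The window is ambiguous rather than contradictory.* In the outcome list, the 24-hour limit can be read as attaching to creatinine alone. Table 3 fits that reading, since its creatinine rows stop at 24 hours while AKI runs to 48. The list is also introduced as a summary that defers to S2. This is a fair reading. But S2 gives no AKI times, AKI is staged from creatinine, and Figure 3e plots creatinine to 48 hours, so the window still has to be stated.

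*The denominator is inferred.* No section says the 48-hour comparison uses only children in PICU. Both nearby S2 rules count missing as normal, and the AKI paragraph borrows the PELOD-2 creatinine thresholds. The SAP also points to posted code, which is not part of these documents. All of this stands: an analysis of children with values only is what the model does by default, not a stated choice.

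*The size is at the upper end.* The calculation carries over the full pilot difference in stay, although the pilot CIs overlap and the trial is sized on 0.2 SD against 0.33 SD seen in the pilot. A smaller difference in early discharge shrinks the bias, and with no difference it vanishes.

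*Little depends on AKI.* The SAP leaves it out of the patient-important outcomes, reports it as descriptive, and treats secondary results as exploratory. This also stands, and it sets the severity.

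**Conclusion.** The point holds as a minor one. The AKI window is inconsistent across the SAP, and a 48-hour AKI comparison is planned with no rule for children already discharged from PICU.

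A reader might go further and infer that a quarter to a third of children will have no 48-hour value and that the comparison is therefore biased against NO. The documents support neither step. The share is model-dependent: about 23–40% in control and 30–45% in NO, assuming the pilot stays carry over and no creatinine is retrieved after PICU discharge. The direction needs three conditions together: only children with a value are analysed, discharged children have less AKI, and early discharge differs between arms.

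Under those conditions the spurious odds ratio is 1.00 to 1.16 at 10% AKI, at most about 0.8 SE, and up to about 1.2 SE at 20% AKI. Counting missing as no AKI gives zero or reversed bias. The primary analysis and sample size are not affected.

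**What to change.** 1. Give the same AKI time points in the SAP outcome list, S2, Table 3 and Figure 3.
2. Make the between-arm comparison the highest KDIGO stage at any scheduled point from PICU admission to 48 hours, or to PICU discharge if earlier. Keep every analysed child in the denominator and adjust for the strata. This follows the convention S2 already uses for LCOS.
3. Keep the time-point rows as description only, showing the number still in PICU at each time and no p-value.

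The cost is wording in the SAP and its tables, with no new data. The SAP requires changes after its publication to be declared, so this one should be. One downside should be stated in the SAP: AKI that arises after an early discharge is counted as none, which can modestly favour the faster-discharged arm. Because values up to discharge are kept, this effect is likely to be smaller than the range in Step 4.
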